
**FIGURE 1 F1:**
[figure not shown]
Overview of ATOP Study Design.

**FIGURE 2 F2:**
[figure not shown]
Timeline.

The qualitative component of the mixed methods design includes patient semi-structured interviews undertaken in the same temporal sequence as the quantitative measures: that is at program entry, during treatment, at discharge, and at each follow-up point. To improve understanding of the treatment setting (i.e., environment and interpersonal interactions), patient interviews are complemented by semi-structured interviews with staff, therapists and healers as well as a contextual description of the Takiwasi treatment center based on existing literature (Mabit and Sieber, 2006; Håland, 2014; O’Shaughnessy, 2017; Mercante, 2013; Dupuis, 2018; Dupuis, 2021; Politi et al., 2019). A sub-project was also initiated part way through project implementation to identify factors associated with non-completion of the program.

The research protocol at Takiwasi was approved by the Comité de Ética PRISMA, *Lima*, Perú.

### Measures

*Quantitative*
Table 1 identifies the quantitative measures used to establish a baseline and measure change over time, as well as treatment motivation at treatment entry, an important potential modulator of outcomes.

**TABLE 1 T1:** Quantitative measures used at baseline and post-treatment.

Quantitative measure	Description
Addiction Severity Index—5th Version (ASI-5)	ASI scores provide a general profile of problem severity in specific areas (drug use, employment, medical and psychiatric disorders, family/social relationships, legal status) and is a proven international standard for treatment planning and post-treatment outcome evaluation. This project employed the Spanish version of the ASI-5 McLellan et al. (1992)
Global Appraisal of Individual Needs –Substance Use Grid	This instrument comprises a small set of items and subscales of a much larger tool used for treatment planning and process and outcome evaluation for substance use treatment - the GAIN-I Dennis, (1999); Coleman-Cowger et al. (2013). The tool is needed to supplement the ASI-5, which does not provide sufficient detail on actual drug use, or treatment history. The GAIN-I, including these sub-scales, has been translated into Spanish. The sub-scales measuring drug use have been adapted to reflect street names of various drugs in the peruvian and Latin american context
Beck Depression and Anxiety Inventories (BDI and BAI)	These are self-administered instruments to measure symptoms of depression and anxiety with 21 items rated on a scale from 0 to 3 Beck et al. (1988); Steer and Beck, (1997). Results are used to classify depression and anxiety as minimal, mild, moderate and severe. They are validated in Spanish Bonicatto et al. (1998); Vega-Dienstmaier et al. (2014)
WHOQOL-BREF—Quality of Life	The WHOQOL-BREF instrument comprises 26 items, which measure the following broad domains: Physical health, psychological health, social relationships, and environment. The WHOQOL-BREF is a shorter version of the original instrument WHOQOL-100 Saxena et al. (2001); The WHOQOL Group, (1998). It assesses the individual's perceptions in the context of their culture and value systems, and their personal goals, standards and concerns. The WHOQOL instruments were developed collaboratively in a number of centers worldwide and have been widely field-tested. The Spanish version has shown good psychometric properties Lucas-Carrasca, (2011); Saxena et al. (2001)
WHOQOL-SRPB—Spirituality, Religiosity and Personal Beliefs	The WHOQOL-SRPB consists of 32 questions, covering quality of life aspects related to spirituality, religiousness and personal beliefs (SRPB). This instrument has been developed from an extensive pilot test of 105 questions in 18 centers around the world. The resulting 32-item instrument represents the finalized version of the WHOQOL-SRPB to be used for field trials. It is available and tested in Spanish Lucas-Carrasco,( 2011)
Treatment Entry Questionnaire (TEQ-9) [BASELINE ONLY]	This brief nine-item questionnaire measures motivation for treatment based on self-determination theory and contains three separate, validated dimensions that relate to identified motivation (e.g., sought treatment because really identified with goals of the program and wanted to make changes); external motivation (e.g., sought treatment because other people pressured); or introjected motivation (e.g., sought treatment because of internal conflict such as to avoid feeling ashamed) Wild et al. (2006); Urbanoski and Wild, (2012); Wild et al. (2016). The instrument has been translated and back-translated to Spanish

*Qualitative* Semi-structured interviews are conducted with recruited program participants at different points: baseline, during treatment, discharge, and each point of follow-up, synchronized with completion of the follow-up quantitative measures. The semi-structured interview guides are included in Supplementary Material.

*Baseline* Information gathered at baseline includes the duration/trajectory of substance use problems and previous formal and informal treatment experiences within this trajectory. Life experiences related to overall health and mental health are also explored. Other areas of questioning include motivations and expectations for the program experience lying ahead, previous experience with ayahuasca, psychedelics, and religious or spiritual practices.

*During treatment and discharge* Since Takiwasi uses ayahuasca in a manner that draws heavily upon Peruvian practices, the specific questions in the interviews during the treatment process reflects these practices. Topic areas for the interview include: general perceptions of the overall Takiwasi treatment experience; the experience with ayahuasca and the importance of subsequent integration activities; and the perception that this has led to changes in the person’s current sense of wellbeing or life satisfaction.

A framework developed previously by Loizaga-Velder and Loizaga (2014) was used to develop the questions that explore the dimensions of the subjective experience with ayahuasca and its therapeutic context. Following this framework, specific feedback is sought on various elements of the overall ceremonial/therapeutic process, including elements of the ceremonial experience (i.e., ceremonial songs [*icaros*], energetic interventions by curandero/a, purging, ritual blowing of tobacco smoke [*sopladas*], *perfumes/aromas*); activities aimed at integration (e.g., psychotherapy or other therapeutic assistance, group sharing); other relevant healing activities such as yoga, exercise or meditation; *purgas* (i.e., therapeutic use of emetic plants); *dietas* (isolation retreats supported by psychoactive plants); shared group experience (e.g., group support, catalyst for group dynamics); and aspects of the treatment milieu (e.g., activities together, gardening, sharing or cooking meals). These areas queried with a five-point rating scale in terms of perceived importance followed by an opportunity for open-ended comment and clarification on the most and least helpful therapeutic elements. The rating scale responses are transferred to the quantitative data file for analysis. Although there was one Likert-type question concerning the Catholic practices of ‘liberation’ and ‘genealogic tree masses’, there were no focused questions or qualitative inquiry concerning perceptions and experience of religious elements (namely Christianity or other syncretic elements) woven into ritual-therapeutic treatments.

The core themes analyzed in the baseline and follow-up qualitative interviews are presented in Table 2.

**TABLE 2 T2:** The core themes analyzed in the baseline and follow-up qualitative interviews.

Data collection phase	Core themes explored
Baseline interviews	Ayahuasca, psychedelics, shamanism (e.g., experience, learnings, worries, expectations before coming to takiwasi)
	Sociodemographic data
	History/context of personal and familial substance use
	Perceptions of mental health and healthcare systems
	Spirituality/religiosity
	Takiwasi-related themes (e.g., reasons for coming; concerns and expectations about treatment; initial perceptions of takiwasi)
	Treatment capital (e.g., previous substance use and/or mental health treatment)
During treatment, discharge, and post-discharge interviews	Meanings/personal significance (e.g., building upon previous treatment experience)
	Program experience (e.g., continuity between ayahuasca sessions; effect on craving; perceived addictive potential; frequency of sessions)
	Recovery process (e.g., perception of benefits, challenges, ability to integrate experiences and learnings into everyday life)
	Satisfaction with services (e.g., overall perception of services received and suggestions for improvement)

#### Study Recruitment and Measuring Treatment Exposure

The status of participant recruitment is summarized below. As of December 17, 2020, a total of 128 participants had completed intake into Takiwasi and were potentially eligible for ATOP. Of these, 42 left the program before participating in any ayahuasca ceremony as part of their treatment. A total of 86 initial participant interview were undertaken at baseline and, of those scheduled for their one-year follow-up (n-60), 48 have completed both the one-year qualitative and quantitative interview, representing an 80% one-year completion rate. The current sample size at 18-months (*n* = 30) and at 24-months (*n* = 25) reflect on-going scheduling and are not reflective of drop = out during follow-up.

As shown in Figure 3, a significant proportion of clients who initiated services at Takiwasi during the study period left the program before any use of ayahuasca (42 of 128 or 32.8%), and therefore, are not eligible for study inclusion. As noted earlier, such high drop-out rates are common in long-term therapeutic community programs and may include reasons that concern the program itself (e.g., too long; content didn’t fit with expectations and personal values); the program environment (e.g., the nature and type of facility or community context); or personal issues (e.g., family or employment concerns made it difficult to continue; psychological issues such as resistance to continued inner work or drug cravings). Some leave treatment programs against advice of program staff and others leave for such personal reasons. This presents a challenge for any observational study with a follow-up component in substance use treatment services since those who finish the program and/or who are located for follow-up may be different in meaningful ways than those who leave the program prematurely.

**FIGURE 3 F3:**
[figure not shown]
ATOP recruitment overview-Takiwasi (as of Dec. 17, 2020).

A related challenge that is important to account for in the study design and analysis is the level of treatment exposure for those formally accepted into the study cohort after the initial ayahuasca experience. We approach the measurement of treatment exposure in two ways. First, with respect to treatment completion the study cohort is divided into three sub-groups: 1) completed treatment; 2) left the program prematurely but voluntarily; and 3) suspended from the program. For the current 12-months sample of 48 clients, the number in each group is 30 (60%); 14 (29%); and 4 (8%), respectively. While all three sub-groups are included in the discharge and follow-up samples, the number of weeks of treatment participation is calculated for each patient. The second approach to measuring treatment exposure is based on an extract of information from the patient files concerning the nature and extent of participation in program activities, for example, the number of ayahuasca sessions, days of dieta, integration sessions with staff. A program participation index will be calculated from these extracted data, also for inclusion in the analysis.

To investigate the potential for response bias in our study sample due to early or subsequent treatment drop-out, a process has been undertaken to locate clients who left prematurely in order to explore reasons for leaving the program. At the time of this writing, the questionnaire has been drafted (see Supplementary Material) and the survey is being mounted for on-line completion. Once finalized, those recruited for the study who have left prematurely will be contacted using the last available email address and a request made for completion of the questionnaire. Also, characteristics of program completers and non-completers will be compared (e.g., age, country of origin; results of the intake psychiatric interview and/or other baseline data).

### Interviews with Managers, Staff and Healers

In addition to the interviews with program participants, semi-structured interviews are conducted with managers, staff, therapists, and healers (see Supplementary Material). This interview captures the person’s role in the center, their professional formation, their own personal religious and spiritual practices, and their use of, and beliefs about, alcohol or other drugs and related treatment practices. Other questions query their training and experience working with ayahuasca, narratives about their own ayahuasca experiences as well as those specifically related to possible links between ceremonial experiences and people’s subsequent change in behavior or habits related to alcohol and other drugs. Narratives also explore their beliefs and experiences regarding the relationship between the different elements of the Takiwasi ‘therapeutic tripod’ in facilitating behavioral changes related to use of alcohol or other drugs.

A total of 17 interviews have been conducted as of December 17, 2020.

### Contextual Description of Takiwasi Center

Consistent with the overall ATOP protocol, the key elements of this contextual description include the program’s *physical and organizational infrastructure* (e.g., physical space, management structure, budget, length of program); *staff/personnel* (e.g., number and type of therapists/staff, the training and experience of curanderos/as and therapists); *prevailing beliefs and mores about addiction* (e.g., curanderos/as and therapists beliefs with respect to causes of addiction, the critical ingredients of effective treatment and definition of good outcome as well as the most common success factors and challenges for people seeking to make changes); *interventions provided*, for example, the combinations of various plants with or without ayahuasca, use of psychiatric medication or other therapeutic techniques, strategies for safety, integration, follow-up and/or continuing care; cultural and community context (e.g., relationship to Indigenous communities, community support and capacity building). See Supplementary Material for guide for site description.

#### Analysis Plan

While the details of the analysis plan differ significantly for the qualitative and quantitative components of the mixed methods, they share several common elements: 1) guided by specific pre-determined research questions in support of the broader project goals identified above; 2) undertaken by two analytic teams working independently and according to their area of expertize (i.e., qualitative or quantitative) but meeting bi-weekly as a unified project team to discuss progress, and develop a consensus on critical questions and issues brought to the meeting from each team.

With respect to the research questions guiding the analysis, these questions were developed by the overall team to create an overarching analytic framework, with the quantitative and qualitative analyses contributing differentially to each question. For example, with respect to Takiwasi patients, both quantitative and qualitative analyses were aimed at the following questions:• What is the individual’s previous experience with substance use treatment and what learnings and challenges are being brought into this new experience at Takiwasi? Is previous treatment experience associated with treatment outcomes?• What is the individual’s situation at treatment entry with respect to physical and mental health challenges and overall life satisfaction? Are baseline physical and mental health challenges associated with treatment outcomes?• What meanings are attached to the overall Takiwasi treatment experience as well as key elements (e.g., treatment milieu, specific medicines, dieta, purging, icaros, therapeutic integration) and how have these meanings evolved during the course of the program? What ratings attached to the significance of these experiences are most closely associated with treatment outcome?

The key questions specific to the quantitative analysis are:• What are the outcomes achieved at 12 months post-discharge (e.g., self-reported reduction in substance use and overall addiction severity; improvements in symptoms of anxiety and depression; change in overall quality of life)?• What factors are independently associated with these 12-months post-discharge outcomes (e.g., treatment motivation; baseline addiction severity or mental health status; discharge status on improvements in mood and anxiety or spirituality).

Examples of questions that are the exclusive focus of the qualitative analysis of patient data include:• What is the person’s subjective understanding of their substance use-related challenges and what is the match between the individual’s perspective and the treatment provided at Takiwasi?• How do clients perceive their recovery process at different follow-up points? What outcomes are reported as being the most meaningful?• Do participants report incorporating learnings and experiences during treatment into their life after discharge?

*Quantitative analytics—Patients* The quantitative analysis team is composed of three team members, aided by an external native Spanish-speaking volunteer. Among the formal team members, one is a native Spanish speaker and two speak Spanish at an intermediate level. The data preparation and analysis will proceed through six steps: 1) preparation of a unified, person-level Excel data file that includes all baseline and subsequent quantitative data points as well as abstracted information from patient files; 2) descriptive analysis of the characteristics of the study sample with frequency distributions and cross-tabulations (see Supplementary Table S1); 3) descriptive analysis of patients’ treatment participation and perceived importance of Takiwasi treatment activities (see Supplementary Table S2); 4) visualization of trends over time across the range plethora outcome measures (See Supplementary Table S3). Importantly, statistical significance testing is not performed on any observed changes over time in these multiple outcomes so as not to violate the principles on which the subsequent stage of multivariate modeling is based (i.e., mitigating increased odds of Type 1 error across multiple, non-theory driven comparisons) (Kuchibhotla et al., 2020); 5) a team-based, measures minimization process so as to reduce the number of predictor and outcome variables based on previous research and a priori conceptual modeling of hypothesized relationships. For example, of the many measures of substance use and problem indicators, one or possibly two primary substance use outcomes measures will be identified, and as well many potential predictor and moderator variables associated with mental health, treatment motivation, treatment participation and ratings of program experience. Finally, 6) Preparation of DAGs (Directed Acyclic Graphs) to conceptually model the hypothesized relationship between predictor and moderating variables and outcome. These DAGs then serve as the basis for multivariate regression modeling (Herman and Robins, 2020). Regression analyses will start with less complex, three to five variable DAGS and build from there based on variance explained through addition of predictors and moderators (Hernan and Robins, 2020) with due consideration for statistical power. See Supplementary Figure S1 for an example of a hypothesized and relatively complex DAG.

Post-discharge outcomes relative to baseline will be analyzed with a generalized linear mixed effects model. Random intercepts (and random slopes where necessary) will be included to account for correlation between observations within study participants. The regression models will also include (potentially time-varying) baseline and within-treatment covariates (e.g., treatment motivation, baseline addiction severity, and number of hours engaged in non-ayahuasca treatment activities such as psychotherapy, group integration, ergotherapy). Statistical inference will proceed in a manner consistent with the DAGs constructed before any models are fit. The relevant parameter and variance estimates associated with all models that are fit will be reported.

*Qualitative analytics—Patients* The qualitative team is composed of four researchers, two of which are native Spanish-speakers, and the other two speak Spanish at an expert level. Qualitative analysis will employ a grounded theory approach (Miles and Huberman, 1994; Strauss and Corbin, 1994), in which the team creates codebooks based on themes that emerge from the interview data with inpatients. Grounded theory approaches work best with relatively open-ended questions and narratives which allow for deep analysis and emergence of key themes, which ultimately become integral to building a case-specific theory about outcomes related to set and setting at Takiwasi. In line with this approach, the original guiding research questions may be modified in an iterative process according to significant themes that emerge in the data.

The team selected a cloud-based qualitative data analysis program (www.dedoose.com) through which they can remotely cross-code data and conduct collaborative analyses. Analysis will focus on several themes guided by the specific research questions, including recovery capital, expectations and perceptions of treatment, spirituality, religiosity, and social influences, among others.

*Integrative quantitative and qualitative analytics—Patients* A framework has been developed to guide the integration of the quantitative and qualitative analysis according to a constant comparative approach to shared evaluation questions. Supplementary Tables S1–S4 illustrate this approach. An important part of this integrative process will involve stratifying the study participants into three groups on the basis of a consensus rating by the project team of each patient’s overall treatment outcome. For convenience purposes, the three groups will be labeled only, as “very poor/poor,” “moderate,” “very good/excellent.” The qualitative themes related to treatment outcome will then be cross-referenced within each of these three groups with the aim being to identify themes reflecting important predictive or moderating factors. These analyses will complement the multivariate modeling based on the DAGs.

*Qualitative analytics* Managers, staff, therapist and healer interviews: As with the patient interviews a set of pre-defined research questions will guide the analysis of these interviews. The primary research focus for these analyses concerns the homogeneity of the therapeutic culture at Takiwasi. Emergent themes will also be identified concerning the convergence and divergence of the Takiwasi therapeutic culture over time. The research questions and their respective aims are:• What are therapists’ main theoretical training and has it influenced their work at Takiwasi (Aim: To identify patterns in practical or theoretical background among practitioners who gravitate toward Takiwasi).• Do therapists utilize their non-psychotherapeutic skills with clients at Takiwasi (e.g., reiki, yoga, etc) (*Aim:* To determine how many alternative healing practices are being applied during clients’ residency).• What are therapists' views on religion? How do their personal views relate to practices at Takiwasi or their relationships with clients (Aim: To explore the subject of institutional religiosity, including the role of Christianity within the context of spirituality).• How has Takiwasi affected therapists' perceptions of care, psychology/psychotherapy, and practice? How did their time at Takiwasi influence their proximate career goals (Aim: To explore the 'training' aspect of Takiwasi and how it influences practitioners).• What are the prevailing views and subjective understanding of addiction and related challenges (Aim: to explore the match between practitioners and the treatment provided at Takiwasi).• Do practitioners link their own experiences with ceremonies and dietas to therapeutic efficacy and/or therapeutic alliance (Aim: To determine the role of ayahuasca in developing a unique kind of therapeutic alliance).• Are there specific aspects of the ayahuasca experience (e.g., dietas, icaros, purging, cleansing/limpiezas, visions, death experiences) that managers, staff, therapists and healers think are particularly helpful for healing? For alcohol and drug addiction specifically (Aim: To explore potential links between prevailing views on program components and treatment outcomes).

The qualitative analysis team will employ a grounded theory approach, creating codebooks based on themes that emerge from the interview data with these Takiwasi stakeholders. In line with this approach, the original guiding research questions may be modified in an iterative process according to significant themes that emerge in the data. The same Dedoose qualitative analysis program will be employed so as to work remotely and collaboratively.

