Our research design was also influenced by several practical considerations. Although Takiwasi serves our purpose as a naturalistic “living research laboratory,” there is not a realistic opportunity to randomly assign patients to alternative treatment conditions, including a no-treatment control group. We also recognize that randomized controlled trials are not without their own challenges (Cohen et al., 2004; Rothwell, 2005; Melberg and Humphreys, 2010; Hyde and Delphin-Rittmon, 2014), especially for complex interventions heavily influenced by set and setting (Stame, 2004). Lack of proximity to enhanced medical facilities also precluded incorporating a neuroimaging component despite early interest among the ATOP team in doing so. Constraints are also imposed by the length of the Takiwasi program (typically nine months) as well as anticipated high treatment drop-out rates, which we forecasted would present challenges in recruiting a study population of sufficient sample size for complex multivariate modeling of treatment exposure and outcome required to identify the most active programmatic ingredients from a statistic point of view. This further highlighted the need for a strong qualitative component to the study design and thoughtful integration of the qualitative and quantitative data.

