Consistent with the above considerations, a research design was formulated that is appropriate and feasible within the Takiwasi context. Figure 1 provides a high-level overview of the various components of the ATOP protocol implemented at Takiwasi with Figure 2 providing a more detailed timeline for the various measurement processes in relation to the various elements of the Takiwasi therapeutic processes. Specifically, a prospective cohort design using a set of core quantitative measures at baseline (i.e., program intake), discharge and 3, 6, 12, 18-months and 24-months follow-ups. The baseline assessment includes a research-based, psychiatric interview to define status regarding substance use and other mental disorders by international standards–The MINI International Neuropsychiatric Interview (Lecrubier et al., 1997; Sheehan et al., 1998). The purpose of this structured interview is for recruitment (i.e., eligibility depends on a research diagnosis of alcohol/drug abuse or dependence and for purposes of sample description and sub-group analysis according to mental health co-morbidity, e.g., co-occurring depressive or anxiety disorder). Following completion of this diagnostic instrument and other aspects of eligibility determination (i.e., assessment of cognitive impairment (Katzman et al., 1983), the remaining baseline measures are administered. These measures cover severity of substance use disorder, quantity and frequency of substance use, motivation for treatment, a range of mental health measures, quality of life, and spirituality. The specific instruments used are identified below according to study phase, all but one of which has been validated in Spanish, that being the Treatment Entry Questionnaire, which the study team translated and back-translated according to accepted international guidelines. Although initially conducted via telephone on Internet (e.g., Skype), the follow-up quantitative data collection was converted to an on-line platform for purposes of cost-efficiency and with personal support available as needed by the respondent. Importantly, all follow-up contacts are initiated and supported by the Research Coordinator who is independent of the programmatic structure of the Takiwasi treatment program itself. First contact with the follow-up Research Coordinator is immediately after inclusion of the participant in the study and then regularly thereafter to book future appointments and maintain accurate information on the client’s living situation.

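### Where change in a measure is regressed on its own baseline, the baseline coefficient is distorted and can read as more severe patients benefiting more

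*Protocol article*

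**What the plan says.** The Analysis Plan's first quantitative question gives the 12-month outcomes, as examples, in terms of change: "self-reported reduction in substance use and overall addiction severity; improvements in symptoms of anxiety and depression; change in overall quality of life". The next question asks "What factors are independently associated with these 12-months post-discharge outcomes (e.g., treatment motivation; baseline addiction severity or mental health status". A question shared with the qualitative team is similar: "Are baseline physical and mental health challenges associated with treatment outcomes".

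The modelling paragraph under Quantitative analytics – Patients states: "Post-discharge outcomes relative to baseline will be analyzed with a generalized linear mixed effects model". It adds random intercepts, with random slopes where necessary, and "baseline and within-treatment covariates (e.g., treatment motivation, baseline addiction severity" among the regressors.

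Table 1 in Measures is titled "Quantitative measures used at baseline and post-treatment". Only the treatment-motivation questionnaire is marked as baseline only, so an outcome scale can also serve as a baseline predictor. Study Design says that "there is not a realistic opportunity to randomly assign patients to alternative treatment conditions, including a no-treatment control group", and that "eligibility depends on a research diagnosis of alcohol/drug abuse or dependence".

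**The concern.** A change score contains the baseline value. Random fluctuation that makes a patient look worse at intake also makes the later improvement look larger, so baseline correlates with change even when severity has no bearing on benefit. Keeping baseline as the first repeated outcome while also entering it as a covariate does not help: the baseline record is then predicted by itself, and the time-by-baseline term carries the same artefact.

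This design is exposed in three ways:

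- Patients are measured at intake with a qualifying diagnosis, and no comparison group shows how much movement would occur anyway.
- The Abstract makes the question of whom the programme works for a stated aim. A false severity gradient would answer it wrongly.
- The Analysis Plan builds up its regression models according to variance explained. A baseline coupled to its own change score would be favoured under that rule.

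Limitations and Conclusion covers brew composition, dose, causality and non-completion. It does not mention regression to the mean.

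**Working it through.** The article states no correlation, standard deviation or power figure for this analysis, so there is no planned figure to reproduce.

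**Inputs**

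- n = 48 with 12-month data (Study Recruitment and Measuring Treatment Exposure).
- Assumed: two-sided 5% level; equal variances at baseline and follow-up, scaled to 1; baseline-to-follow-up correlation ρ between 0.3 and 0.8.

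**Algebra.** Take a scale on which high is worse, with baseline Y0, follow-up Y1 and improvement I = Y0 − Y1.

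- Cov(Y0, I) = 1 − ρ and Var(I) = 2(1 − ρ).
- Slope of I on Y0 = 1 − ρ.
- Corr(Y0, I) = (1 − ρ)/√(2(1 − ρ)) = √((1 − ρ)/2). For change defined as Y1 − Y0 the sign is negative.
- Critical |r| at n = 48 is t/√(t² + 46) with t = 2.013, which gives 0.2845.

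**Simulation.** n = 48, 20,000 runs per ρ, no true link between severity and benefit. The last column is the chance of a significant result in the direction of more severe patients improving more.

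| ρ | Built-in correlation (absolute) | Extra improvement, +1 SD vs −1 SD at baseline: 2(1 − ρ) | Significant |
|---|---|---|---|
| 0.3 | 0.59 | 1.4 SD | 99.6% |
| 0.4 | 0.55 | 1.2 SD | 98.7% |
| 0.5 | 0.50 | 1.0 SD | 96.0% |
| 0.6 | 0.45 | 0.8 SD | 90.3% |
| 0.7 | 0.39 | 0.6 SD | 78.9% |
| 0.8 | 0.32 | 0.4 SD | 59.4% |

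At ρ = 0.5 baseline explains (1 − 0.5)/2 = 25% of the variance of change with no real effect.

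**Baseline as repeated outcome and covariate.** A random-intercept model with two occasions and a time-by-baseline term (150 runs per value) gave mean interactions of −0.68, −0.50, −0.30 and −0.18 at ρ = 0.3, 0.5, 0.7 and 0.8. They were significant in 99%, 97%, 83% and 53% of runs. With 150 runs the last figure has a standard error of √(0.53 × 0.47/150), about 4 percentage points.

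**A contrast on the same data.** Relating change to the mean of baseline and follow-up (Oldham's method) gave false positives in 4.7% to 5.1% of runs for ρ from 0.3 to 0.8. The excess therefore comes from using baseline itself as the regressor.

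**Other predictors.** With baseline in a linear model, regressing change or follow-up level gives the other predictors coefficients of identical size (largest difference 6 × 10⁻¹⁵). Only the baseline coefficient changes meaning, from 1 − ρ for improvement to ρ for level. Dropping baseline would do harm: a predictor with no effect, correlated 0.4 with baseline, acquires a slope on improvement of 0.4 × (1 − 0.5) = 0.20 at ρ = 0.5.

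**The case against.** The strongest reply is that the article does not commit to regressing a change score on its own baseline. The outcomes are listed as examples in a research question. The Analysis Plan leaves the one or two primary substance use measures to a later selection step and the predictor–outcome pairings to causal diagrams drawn before fitting. Addiction severity and quantity of use come from different instruments. The mixed-model sentence can also be read as post-discharge level adjusted for baseline, which is what is recommended here. All of this stands, and it makes the point conditional.

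The size is conditional too. Suppose baseline variance is 1 (of which 0.2 is error), follow-up error variance is 0.2, and individual response has variance 0.5 independent of true severity. Follow-up variance is then 0.8 + 0.5 + 0.2 = 1.5, ρ = 0.8/√1.5 = 0.65, and the correlation of baseline with change is −0.2/√0.9 = −0.21. That is below the 0.28 threshold, whereas the equal-variance formula would give −0.42.

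A reader might infer that a severity gradient is certain to appear, that every predictor is biased, or that adjusting for baseline is itself the error. The documents and the arithmetic support none of these. Nor does the article say that it will interpret the baseline coefficient as differential benefit.

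It might also be said that the form of the response is a detail for a fuller plan. But the article itself gives the outcome scale, the model class and the covariates, and their plain combination leads to the problem. Drawing causal diagrams first does not remove it, and the general caution about causality does not address it.

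**Conclusion.** The point holds in conditional form. The wording allows, and on its natural reading suggests, a model that relates change in a measure to its own baseline. A model with baseline as both repeated outcome and covariate fares no better. In either case the baseline term is misleading and, without a control arm, can pass for evidence that sicker patients gain more.

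With equal variances and ρ from 0.3 to 0.7, the built-in correlation is −0.59 to −0.39 against a critical value of 0.28 at n = 48. The chance of a spurious significant gradient is then 99.6% to 78.9%, falling to 59.4% at ρ = 0.8. It is weaker if follow-up variance exceeds baseline variance, or if predictor and outcome are different measures. More patients would not cure it, because the critical value falls with n and the built-in correlation does not.

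The damage is confined to the coefficient of the measure's own baseline, or its interaction with time. In the comparison of change with level, the other predictors are unaffected once baseline is in the model. This should be corrected before the first one-year analysis, but it does not undermine the study as a whole.

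**What to change.** In the mixed-model paragraph of the Analysis Plan:

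- For the predictor models, replace outcomes expressed relative to baseline with the post-discharge level of each measure. Enter that measure's own baseline value as a covariate, and do not also keep baseline as a repeated outcome in the same model.
- State that the baseline coefficient is prognostic, describing how later status tracks intake status, and will not be read as showing who benefits more.
- Report mean 12-month change with a 95% confidence interval from a separate repeated-measures model that includes the baseline occasion as an outcome but not as a covariate. Add that, without a control group, this change may include regression to the mean.

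The cost is a few sentences and no new data. The real concession is that predictors of improvement become predictors of 12-month status given baseline, and the related key questions should be reworded to match.
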